#### Existing interventions for medical trauma

The risk of adverse mental health outcomes among paediatric burn patients makes the implementation of timely and effective interventions for these children imperative. Several trauma-informed interventions have been developed and tailored to other populations, with some treatment types involving exposure to the original traumatic event [26]. For example, Narrative Exposure Therapy (NET) [27] enables patients to retell their trauma-narrative, typically while engaging in trauma-focused cognitive-behavioural therapy (TF-CBT). The retelling of the trauma-narrative allows patients to habituate to their traumatic experience and facilitates the guided analysis of painful emotions, leading to emotional recovery from the trauma. Studies have validated the efficacy of narrative therapy in traumatised child populations, demonstrating that it is not only an effective model of treatment [28], but can also be superior to alternative interventions [29]. Another effective trauma-focused intervention is the Skills for Psychological Recovery (SPR) intervention, developed by the National Child and Traumatic Stress Network and National Centre for PTSD’s [30]. Based on extensive research surrounding the most common emotional and behavioural reactions following natural disasters, SPR is a brief and effective intervention designed to promote healthy psychological recovery after traumatic experiences [31]. Although effective, trauma-focused therapies such as TF-CBT and SPR have not been trialled in paediatric burn populations.

Despite evidence demonstrating that a burn injury can be a traumatic event that can impact mental health, mental health is often overlooked in post-burn recovery. There are a few psychosocial interventions which seek to fill this gap, but most are focused on distraction from painful procedures rather than focusing on the recovery following the burn [32]. The authors of this systematic review found that: a) existing interventions only draw from singular techniques (e.g., CBT and virtual reality [VR]) to deliver psychosocial care which has shown mixed results, and b) there is no individual technique which suits the needs of all participant demographics. The current intervention fills this gap through a co-design process with community stakeholders (caregivers, young people, researchers, and clinicians) who have determined that a combination of individual techniques (TF-CBT, SPR and NET) was important to include in this pilot intervention.

Co-design is participatory research that actively involves stakeholders in the development of an intervention to meet the needs of people it seeks to assist [33]. This collaborative approach can improve the creative process of developing an intervention, improve service delivery, and acceptability amongst its users [34]. Co-designed interventions have previously been used to map children and families’ emotional journey following a burn injury [35], as well as in the development of other mental health interventions following childhood medical trauma [36]. The current paper describes the process used for community consultation and collaborative adaptation of the proposed intervention, and the piloting of this intervention with children and young people who have experienced a burn and clinicians. This pilot study can help us understand if the methods and procedures are feasible and if the sessions designed are appropriate and accepted by participants. At a broader level, this study will provide paediatric burn health services and clinical teams, a program that adopts a trauma-informed approach to care to recognise and respond to trauma and ease the recovery journey. Early intervention is needed to reduce the impact of poor mental health and allowing for more effective healthcare pathways for paediatric burn patients.

## Objectives

The project seeks to further elucidate sources of stress and trauma that accompanies a burn injury and to develop a much-needed trauma-focused psychosocial intervention through co-design to maximise its impact in this population. We also seek to pilot test and evaluate this intervention to support resilience and promote positive mental health recovery in children and adolescents who have sustained a burn injury. The specific objectives of the intervention are to:

Undertake preliminary analyses to explore the association of mental health indicators with burn characteristics and demographics.Collect pilot data to determine the appropriateness of the developed intervention by investigating the changes in mental health indicators pre- and post-intervention.

## Methods

### Study design

This study is a non-randomised, pre-post, cohort study which seeks to determine the potential effects of a psychosocial intervention. We use convenience sampling, with data collected from age-appropriate questionnaires at four time points: Time 1 (T^1^): baseline assessments; Time 2 (T^2^): post intervention assessments; Time 3 (T^3^): 6-month follow up assessments; Time 4 (T^4^): 12-month follow up assessments. Randomisation and blinding are not relevant in this pilot study due to the single intervention arm, where intervention’s absolute effect on the participants across time is the primary interest to determine the appropriateness of the intervention content [37].

### Ethics

The study has received ethics approval from the WA Child and Adolescent Health Service (CAHS) Human Research Ethics Committee (HREC) and Research Governance Office (RGS4669). Any intervention protocol modifications will be approved by these committees and communicated to the participants.

### Stage 1: Co-design process

Caregivers and adolescents were invited to participate in an interview or focus group and were provided the opportunity to (1) discuss the traumatic impact of a paediatric burn injury and (2) evaluate the proposed intervention. Participants were recruited from the Stan Perron Centre of Excellence for Burns and the Perth Children’s Hospital (PCH) burns outpatient clinic. The following groups took part in this co-design process: caregivers (n = 11, dyadic interview = 1, interviews = 9) of children aged 4–12 years who have sustained a burn injury and adolescents (n = 7, interviews = 7) (aged 12 years and older) who have sustained a burn injury. In addition, clinicians (n = 5, focus group = 1) from the Stan Perron Centre of Excellence for Childhood Burns and/or the PCH burns outpatient unit participated in a focus group to provide feedback on the design and structure of the intervention. Due to COVID-19 restrictions at PCH, all interviews and focus group were conducted online as semi-structured interviews using the Microsoft Teams platform.

This co-design process was conducted: (1) to provide valuable insight into the traumatic nature of acute paediatric burns from the perspective or caregivers and adolescents and (2) determine the acceptability of our intervention from the perspective of adolescents, caregivers and clinicians. Audio was recorded during focus groups and interviews to ensure all participant contributions were documented. To explore the traumatic nature of a paediatric burn on the family from a child’s [13] and caregiver’s perspective [21], recordings were transcribed and de-identified. Furthermore, to determine the acceptability of the proposed intervention, the intervention outline and resource materials were presented to all participants, after which, they were asked a series of questions to provide feedback for the intervention. All intervention amendments and adaptations suggested by caregivers, adolescents and clinicians were agreed upon by the end of the collaborative design session. Participants were given the opportunity to view the final developed intervention upon request.

### Stage 2: Intervention

#### Participants

*Participant eligibility criteria*. Eligibility will include school aged children aged 6–17 years who have sustained a burn injury and attended the Stan Perron Centre of Excellence for Childhood Burns at PCH in the previous 12 months, and their caregivers. Participants must be fluent in speaking and reading the English language (due to limited funding for interpreters and translators, alongside a lack of validated measures for other languages). Participants must also have access to an internet connected device (e.g., computer, tablet, mobile phone) to facilitate the intervention sessions and study surveys.

*Exclusion criteria*. Children aged 0–5 years will be excluded from the study as sessions for children aged 0–5 would be a family intervention involving the caregiver, rather than a child-directed intervention. Children presenting with an intentional burn injury (i.e., burn injuries that are self-inflicted or inflicted by others to cause harm [38]), or who have a diagnosed cognitive impairment (e.g., traumatic brain injury) that means they are unable to attend/understand the intervention content will be excluded from this study. Caregivers who have a known substance abuse issue or are unable to appropriately engage in the intervention due to pre-existing severe psychological distress will also be excluded. The exclusion criteria will be identified during the screening process, through discussions with the clinical and PCH burns research team and recorded patient medical notes on the Burns Information Management System (BIMS). If not previously disclosed, this information can also be identified in the demographic questionnaire provided to participants during the baseline screening process. Levels of understanding of the requirements for research participation will be determined by the completion of the consent process.

*Recruitment and consent*. Participants will be recruited by a member of the research team at their outpatient burns clinic appointment at PCH. Convenience sampling will be used to recruit participants into this pilot study from PCH due to its paediatric burn’s outpatient clinic’s proximity and accessibility for the research team. PCH oversees the management of most paediatric burn cases across WA, especially for more severe cases.

Eligible participants who are approached will be given a Participant Information Sheet (PIF), will have the project explained verbally by the researcher, and will be given the opportunity to ask any questions. Full informed consent will ensure that the caregiver understands the adequate dosage of intervention that needs to be provided to see sufficient therapeutic gains and that the caregiver provides commitment (and that of the child’s) to the process of intervention in order to minimise attrition. Informed consent will be sought from young people aged 12 years and older and their caregivers via REDCap [39]. Children aged 6–11 years old will be provided with an age-appropriate verbal explanation of the study by the researcher. The researcher who conducts the consenting process will also sign a consent form, confirming they have checked participants’ identity and have given a verbal explanation of the study to the participant. In addition to the information obtained during T^1^ (baseline assessments), caregivers will be asked to consent to their child’s medical records (obtained from the Child Adolescent Health Service [CAHS] database) being used in the current study. Specifically, the PIF asks caregivers if the researchers can access the following information about their child: location of the burn, severity of the burn, date of burn event, time spent in hospital following burn. This information will be used to further describe the demographics of study participants.

*Sample size*. There will be an active recruitment process until the proposed sample size of 40 children has been met. This is a novel intervention for paediatric burn patients, and thus similar outcome analyses have not been published, making sample size estimation difficult. Sample size calculations are not required for all pilot studies, however they must be representative of the target study population and inclusion criteria [40]. Thus, this pilot study has a sample size of 40 children, that is representative of the paediatric burns population at our study site and participant eligibility criteria. Having a sample size of 40 children will ensure this study is feasible and accounts for a 20% attrition rate.

Furthermore, one caregiver from each participant must be involved in the study. Caregivers in this study will not participate in the intervention but will complete specific questionnaires that will be self-assessed or completed on behalf of their child, for cross-informant reporting for their children’s mental health status and outcomes throughout the study.

## Overview of intervention design

The piloting of the intervention will be delivered by a trained member of the research team with experience working in mental health settings. Sessions will be held weekly or fortnightly (based on participant availability) for a total of six sessions, with each session taking approximately 45-minutes to complete. Based on findings from the co-design process and current evidence-based practice, the intervention sessions were designed to contain skills included in TF-CBT, SPR and NET. The structure and content of sessions were informed by the common principles co-existing across evidence-based trauma-focused interventions [27] including: psychoeducation (first step in treatment) [27, 41–43]; coping skills such as relaxation skills (e.g., mindfulness) [44]; creating a trauma narrative [27] (the majority of trauma-informed therapies encourage the completion of a trauma narrative) [44, 45]; cognitive restructuring [27, 46]; and creating a posttreatment plan [27]. Due to the resilience based focused, this mental health recovery program was named ‘The Wellbeing Program’.

Based on the co-design process and due to the ongoing restrictions and service changes at PCH due to the COVID-19 pandemic (such as in-person appointments moving to Telehealth), the sessions will be delivered via the video communications platform ‘Microsoft Teams’ (Version 16.2.8). The online format allows the intervention to be more accessible to patients who live a significant distance away from PCH (i.e., regional/remote). If restrictions are eased, the research team will offer face-to-face sessions with participants, which will be scheduled to roughly coincide with the child’s outpatient appointments with the burn unit at PCH. However, opting only for a face-to-face intervention will restrict the number of participants who may be willing to participate.

Participants that choose to have face-to-face sessions rather than online, will be reimbursed for parking costs. Session structure and design will remain the same. For most caregivers who participated in the co-design process, online program delivery was the preferred method due to convenience and logistics. Additionally, the total number of sessions was reduced from nine to six, and further activities were incorporated to ensure children and families remained engaged for the duration of the session. With caregivers being a crucial part of a child’s burn recovery journey, their involvement in the sessions was favoured, namely, to support a shifting in feelings of guilt and blame by assisting in their child’s support process. Furthermore, the feedback from clinicians identified the impact that paediatric burns have on the child and their caregiver, and the support required throughout their burn journey. Clinicians discussed the repetitive trauma that families undergo during dressing changes, including the physical pain the child endures and the anxiety children and caregivers go through during the hospital admission period. Thus, a key focus of this intervention is to acknowledge the challenges families face, identify how far they have come, and support them through the recovery process. Additionally, clinicians recognised how the capacity to recover is dependent on child premorbid functioning and identified the importance of screening and intervening early to provide a comprehensive overview of both physical and mental health factors. With resilience building being a core focus of the intervention, clinicians reinforced how the intervention must be tailored to suit the needs and personalities of each child. Clinicians also expressed their concerns in the suitability of session content for younger children and the limited ‘fun’ aspects, therefore content was reviewed and developed for two separate cohorts (6–12 years and 13–17 years old) and additional activities were added (e.g., games such as snakes and ladders). An intervention session plan is outlined in Table 1.

**Table 1 pone.0294237.t001:** Revised intervention session plans.

Session	Overview
**1. Introduction, Assessment, Information Gathering**	Session aim: To establish rapport, formulate appropriate matching of skills to presenting problems and orient the subsequent visit on the highest priority areas. Review screening measure results. Introduce the caregiver booklet: A caregiver resource is provided to include information about the child moving through various types of responses to different situations and stages of healing. This resource will enable caregivers to be aware of these processes and how to best support their child. Introduce the child booklet: The child resource will be used across the sessions to complete activities, and the caregiver resource will compliment this by providing some context on the activity and the benefit it will have on their child. The facilitator explains the program, including the “why” and “how’s”. Participant intake progress notes for ages 6–12 (see S1 Table) and 13–17 years will be used to identify the most pressing needs. The first strategy that is introduced (i.e., emotional wellbeing, interpersonal connections) will align with this. The interview structure is the same for both age groups, however the language has been modified to be age appropriate. NB: For all ages, sessions 2–5 will have age-dependent activities, however the session structure will be consistent.
**2. Managing reactions (Behaviour)**	Introduction and orientation to the session; age-dependent language and use of child booklet for discussion. Psychoeducation and link to activity depending on each age. CBT introduction and link to relevant activity. Breathing activity and reaction management strategy. Homework allocation if specified in the booklet. Summary and discussion of any points that are unclear to the child/caregiver.
**3. Managing reactions (Thoughts)**	Introduction, wellbeing check, and homework revision if required. Orientation to session. Thought introduction and link to relevant activity. Homework allocation if specified in the booklet. Summary and discussion of any unclear points.
**4. Identifying and Bolstering coping skills**	Introduction, wellbeing check, and homework revision if required. Orientation to session. Coping, avoidance and withdrawal explanation and discussion. Respective booklet used for discussion. Coping activity to support the child’s understanding of healthy and unhealthy coping processes. Homework allocation if specified in the booklet. Summary and discussion of any unclear points.
**5. Problem solving**	Introduction, wellbeing check, and homework revision if required. Orientation to session. Introduction to worrying versus problem solving. Problem solving activity. Homework allocation if specified in the booklet. Summary and discussion of any unclear points.
**6. Preventing setbacks**	Introduction, wellbeing check, and homework revision if required. Orientation to session. Discussion of previous sessions. Development a story of what the child/adolescent did/enjoyed prior to their burn. Development a story of what happened during the burn (who, what, when, where), highlighting successes (what helped). Development a story of what the adolescent wants for their future, highlighting successes (what helped after the burn; including techniques taught over the program and strengths identified to date). Reading of the story aloud. Summary and discussion of any unclear points. Questionnaires will be re-administered.

### Instruments

During baseline assessment (T^1^), a demographic questionnaire will be administered to adolescents (12–17 years old) and all caregivers to capture their age, gender, and any mental health conditions they or their child have been diagnosed with prior to and after the child’s burn injury. For children aged 11 years and younger, caregivers will capture this information on their behalf. The potential effects and feasibility of our intervention will be assessed via the selection of measures from the screening procedure with the aim of determining whether the current content of the intervention can cause change in mental health outcomes for participants [47]. Children aged 8–17 years (self-report) and caregivers (caregiver report and self-report) will complete a range of screening tools at pre- and post-intervention (T^1^ and T^2^ respectively), as well as at 6- and 12-months post-intervention (T^3^ and T^4^ respectively), which will be used as outcome measures of the intervention and to assess mental health (Table 2).

**Table 2 pone.0294237.t002:** Child and caregiver screening measures used in The Wellbeing Program.

Construct	Measure	Participants age range	Reliability	Items (number and response procedure)	Additional information
**Internalising and externalising behaviours**	The Strengths and Difficulties Questionnaire (SDQ) [53].	Caregiver report: On behalf of children aged 6–17 years Self-report: Children aged 11–17 years only	Test-retest reliability rho = .62 and internal consistency α = .73	25 items	The SDQ is a screening tool that can be used as a treatment outcome measure for children and adolescents [53]. The SDQ asks about attributes such as emotional symptoms (5 items), conduct problems (5 items), hyperactivity or inattention (5 items), peer relationship problems (5 items) and prosocial behaviour (5 items) [53].
**Child behavioural and emotional issues**	The Child Behaviour Checklist (CBCL) [54]	Caregiver report: On behalf of children aged 6–17 years	Test-retest = .73–0.94, internal consistency C = .63 -.97), and inter-rater reliabilities = .57 -.88	113 items Likert scale 0 (not true, as far as you know) to 2 (very true or often true)	The CBCL is used to detect changes after participating in short and long behavioural and mental health interventions [55–57]. The CBCL measures child and adolescent mental health in the areas of anxiety, depression, somatic complaints, social problems, thought problems, attention problems, rule breaking and aggressive behaviour.
**Adolescent behavioural and emotional issues**	The Youth Self-Report (YSR) [58]	Self-report: Children aged 11–17 years only	Test-retest = .67 -.91, and internal consistency (α = .55 -.95	118 items Likert scale 0 (not true) to 2 (very true or often true)	The YSR is used as a mental health outcome measure and has reported tests of significance [59]. The YSR assess the same domains as the CBCL.
**Anxiety**	The State-Trait Anxiety Inventory (STAI) [60]	Self-report: Children aged 12–17 years only Caregivers	Test-retest reliability r = .65 -.75 and internal consistency α = .86 -.95	40 items Likert scale 1 (not at all) and 4 (very much so)	STAI has 20 items that indicate how an individual feels in the present moment (state) and how they generally feel (trait). Since 1970 the STAI has been used in a range of research and clinical practices to evaluate processes and outcomes in behavioural and cognitive treatments and interventions [61].
**Anxiety**	The State-Trait Anxiety Inventory–Child report (STAI-CH) [61]	Self-report: Children aged 9–12 years only	Test-retest reliability r = .16 -.61 and internal consistency α = .78–87	40 items Likert scale 1 (hardly-ever) and 3 (often)	STAI-CH is the child version of the STAI and assesses the same domains.
**PTSD symptoms**	The Child PTSD Symptom Scale for DSM-5 (CPSS-5) [62]	Self-report: Children aged 8–17 years only	Test-retest reliability r = .80 and internal consistency α = .92	27 items Likert scale (20 items) frequency and severity from 0 (not at all) to 4 (6 or more times a week /severe). 7 functioning items (yes/no)	The CPSS-5-SR measures PTSD severity. The CPSS-5-SR has a cut-off score of 31 to determine a probable PTSD diagnosis [62].
**PTSD symptoms**	The PTSD Checklist for DSM-5 (PCL-5) [63]	Self-report: Caregivers	Test-retest reliability (r = .74 -.85) and internal consistency α = .94	20 items Likert scale 0 (not at all) to 4 (extremely)	The PCL-5 is used to monitor symptom change during and after treatment, screening individuals for PTSD and making a provisional PTSD diagnosis. Weathers et al [63] suggests using the DSM-IV criteria to determine reliable (5–10 point) and significant changes (10–20 point) [64].
**Stress**	The Perceived Stress Scale (PSS-10)	Self-report: Children aged 11–17 years old only Caregivers	Internal consistency α = .78	10 items Likert scale 0 (never) to very often (4)	The PSS-10 measures individual stress levels. It has been used as an outcome measure to identify reductions in stress scores from a 10-week stress reduction program [65] and clinical studies [66].
**Stress**	The Parental Stress Scale (PSS) [67]	Self-report: Caregivers	Test-retest reliability over a 6-week period r = .81 and internal consistency α = .83	101 items Likert scale 1 (strongly disagree) and 5 (strongly agree).	The PSS has been used to measure change in parental stress levels following individual and family interventions [68]. Thus, comparisons of mean before and after scores can be made.
**Resilience**	The Connor-Davidson Resilience Scale (CD-RISC) [69]	Self-report: Children aged 10–18 years only Caregivers	Internal consistency α = .84 -.86	10 items Likert scale 0 (not true at all) to 4 (true nearly all the time)	Many studies have used the CD-RISC to assess change in resiliency during treatment including psychotherapy [70, 71] and other interventions, such as stress-management [72–74] or resilience-building [75].

Due to age range restrictions of the selected questionnaires, children aged 6–7 years old will not need to complete any self-reported questionnaires therefore, only caregiver reports will be collected for this age range. The selected questionnaires show mixed reliability among the younger age groups and often relied on parental or researcher administration to show success which is not always logistically possible [48–50]. To ameliorate this limitation, and to complement the self-reported measure, all caregivers of children in this study will be required to complete The Strengths and Difficulties Questionnaire (SDQ) and Child Behaviour Checklist (CBCL) that asks questions and statements about their child (caregiver report). Our previous research has highlighted how paediatric burns can be inherently traumatic for caregivers, particularly mothers, and thus can adversely affect their mental health outcomes [21]. Therefore, parental screening measures are included in this study despite children and adolescents being the primary target of this intervention.

All outcome measures, excluding the SDQ, will be completed at all four timepoints (T^1^, T^2^, T^3^, T^4^) and will take approximately 30–60 minutes to complete at each timepoint. The SDQ will be completed only at T^1^, T^3^ and T^4^ timepoints as the online version of the SDQ asks responders to recall information from the “previous six months”. The SDQ will be completed on the SDQ online survey platform, and all remaining measures will be completed online via REDCap [51, 52]. Permission to use the measures has been granted by the authors and/or owners. All screening measures will be administered by a research team member under the supervision of a Child and Adolescent Psychiatrist and have received training in all the data collection and analysis procedures.

A range of valid and reliable child and caregiver directed screening measures will be collected (Table 2). Questionnaire suitability was determined based on validity, reliabilities, and responsiveness to change. Age-appropriate screening measures will be used to identify changes in a child’s internalising and externalising behaviours (SDQ), general behavioural and emotional issues (CBCL and Youth Self Report), anxiety levels (The State-Trait Anxiety Inventory [STAI] and The State-Trait Anxiety Inventory—Child report [STAI-CH)), PTSD symptoms (The Child PTSD Symptom Scale for DSM-5 [CPSS-5] and The PTSD Checklist for DSM-5 [PCL-5]), stress (The Perceived Stress Scale [PSS-10] and The Parental Stress Scale [PSS]) and resilience (The Conner-Davidson Resilience Scale [CD-RISC]) after participating in this intervention.

In addition to the assessments, participant intake progress notes will be used during the first session by the facilitator to understand the child’s most pressing needs and build rapport with the child (S1 Table). The notes will provide a thorough picture of the client needs at the time of intake including their burn experience, personal and social history, mental health history, current symptoms and concerns, previous treatment received and family environment. The intake notes will remain the same for both age groups however, the facilitator can modify the wording of the questions to suit the 13–17 year old age group (e.g., Question 1: Can you talk to me about your burn experience?).

At the end of each session, adolescents (13–17 years) will also be sent an evaluation survey by text message to identify 1) if they enjoyed the session (Yes or No) and 2) how helpful they found the session (scale 1–5). Immediately after the final session another evaluation survey will be sent to adolescents to identify 1) what session was the most useful (ranking from 1–6) and 2) what their overall rating of the program is. This will provide children with the opportunity to provide feedback, identify participant responsiveness and ensure high quality program delivery for future interventions. Fig 1 reflects participant involvement in this intervention.

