Individual-based Change Statistics (IBC) such as the Standardized Individual Difference or the Reliable Change Index will also be used, as these have been shown to be effective in detecting change in clinical populations and do not require arbitrary cut-off points [77]. Additionally, we will analyse the feasibility and acceptability of the intervention via adherence and compliance to the program, attrition rates and uptake of recruitment and post-session ratings (children aged 13–17 years only). Pilot feasibility studies are able to provide information on consent rates, treatment compliance and methods of outcome measurement to assess the potential efficacy of a novel intervention [78]. The results of the analysis will enable the research team to identify participant behaviour and attitude changes, improvements in mental health, and determine if our intervention design is suitable for a future roll-out [47]. Data cleaning and statistical analyses will be performed in Stata/SPSS [79].

We intend to use restriction of enrolment and statistical analyses methods to control for confounding factors. Due to the preventative and non-clinical nature of this intervention, it was imperative that we incorporated screening measures and methods which would exclude young people and/or their carers who have existing mental health concerns. Furthermore, we intend to apply correction methods (e.g., stratification by age group) as needed to further delineate the effects of the intervention based on other participant characteristics.

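### The overall programme rating and session ranking are sent only after the final session, so both reflect only adolescents who reach it; session ratings and attrition only partly offset this

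*Protocol article*

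**What the plan says.** The programme runs "for a total of six sessions, with each session taking approximately 45-minutes to complete" (Overview of intervention design). The Instruments section describes two kinds of participant feedback, both for ages 13–17 only.

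- **After each session:** "At the end of each session, adolescents (13–17 years) will also be sent an evaluation survey by text message". The two items are "if they enjoyed the session (Yes or No) and 2) how helpful they found the session (scale 1–5").
- **After the last session:** "Immediately after the final session another evaluation survey will be sent to adolescents". The two items are "what session was the most useful (ranking from 1–6) and 2) what their overall rating of the program is". No response scale is given for the overall rating.

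The analysis section (Data preparation and statistical analysis) will assess "feasibility and acceptability of the intervention via adherence and compliance to the program, attrition rates and uptake of recruitment and post-session ratings". It does not name the end-of-programme rating separately. The sample-size paragraph allows for 20% attrition in 40 children, without saying at what stage of the study it is expected.

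**The concern.** In a pilot, an overall rating is useful if it covers everyone who tried the programme. Here the request is triggered by the final session, so the people asked are selected by having stayed. If those who leave tend to be less satisfied, the reported rating is higher than it would be among all starters, and it rises as more dissatisfied adolescents leave. The ranking has the same limit: adolescents who stopped after an early session have no say in which sessions were most useful.

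This matters because the article gives the pilot the task of showing whether the sessions are appropriate and accepted (end of the Introduction), whether the design suits a future roll-out (analysis section), and what to modify before a larger trial (Strengths and limitations). It is also a collection rule, not an analysis choice. A later analysis plan cannot recover a rating that was never requested.

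**Working it through.** **The plan's own figure.** The article states no figure for the acceptability ratings, so there is nothing to reproduce. The only related numbers are 40 children and 20% attrition (40 × 0.80 = 32 remaining; the 32 is not stated in the article).

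**Step 1. Who is sent what.** An adolescent who leaves after session *k* (*k* from 1 to 5) has been sent *k* session surveys, no overall rating and no ranking. One who misses a middle session but attends the last is sent everything except the survey for the missed session.

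**Step 2. How many are affected.** The age split is not given. If 10 to 25 of the 40 are aged 13–17 (assumed range) and 20% of them stop during the sessions (assumed), then 10 × 0.20 = 2 to 25 × 0.20 = 5 adolescents are never asked for an overall rating.

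**Step 3. Bias in the overall rating.** Let *d* be the proportion stopping, and F and S the mean ratings of finishers and stoppers. The mean over all starters is (1 − *d*)F + *d*S. The finishers-only mean exceeds it by *d*(F − S). Assume a 1–5 scale, as for session helpfulness:

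| *d* (assumed) | F − S = 0 | F − S = 1 | F − S = 1.7 |
|---|---|---|---|
| 0.20 | 0 | 0.20 | 0.34 |
| 0.30 | 0 | 0.30 | 0.51 |

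For example, F = 4.2 and S = 2.5 with 12 finishers and 3 stoppers gives (12 × 4.2 + 3 × 2.5)/15 = 3.86 over all starters, against 4.2 in finishers.

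The overall rating's scale is not stated, so the same formula is also shown for a proportion favourable. With *d* = 0.20, 90% favourable in finishers and 90%, 60%, 30% or 0% in stoppers, the all-starter value is 90%, 84%, 78% or 72%. The finishers-only figure is then too high by 0, 6, 12 or 18 percentage points.

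**Step 4. How far session ratings compensate.** If every stopper leaves after *k* sessions and finishers attend all six, stoppers receive the share *dk* / (*dk* + (1 − *d*) × 6) of all session-survey invitations. With *d* = 0.20:

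| Sessions attended by stoppers (*k*) | 1 | 2 | 3 | 4 | 5 |
|---|---|---|---|---|---|
| Share of invitations | 4% | 8% | 11% | 14% | 17% |

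Stoppers are present, but always below their 20% share of starters, and far below it if they leave early.

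**Step 5. Trend across sessions.** With F = 4.2, S = 2.5 and *d* = 0.20, suppose everyone rates session 1 and no stopper attends session 6. Mean helpfulness then moves from 0.80 × 4.2 + 0.20 × 2.5 = 3.86 at session 1 to 4.2 at session 6, although nobody has changed their view.

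**The case against.** The strongest reply is that dropout is already part of the evidence. Surveys follow every session, so those who leave contribute ratings up to and including the last session they attended. The analysis section also counts attrition, adherence, compliance and uptake as evidence on feasibility and acceptability. If dissatisfied adolescents leave, a high overall rating would appear beside high attrition. This stands. A reader might infer that the whole acceptability result comes from those who liked the programme enough to finish, and the document does not support that. What remains is that session items ask about one session at a time, early leavers supply few of them, and attrition records that someone left but not how they judged the programme.

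Two further inferences also go too far.

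- **That only those who attended all six sessions can answer the final survey.** The text ties it to the final session, not to full attendance.
- **That the trial collects no reason for stopping.** The article describes none, but it is a condensed account. It refers to an ethics-committee protocol and a standard operating procedures document that are not shown, and its participant-involvement figure is also not shown.

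It is also fair to say that the illustrated sizes rest on assumed ratings, and that the 20% allowance may cover loss through the 12-month follow-up and not the session period alone.

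**Conclusion.** The point holds in a limited form. As described, the overall rating and the ranking come only from adolescents who reach session 6. The overall rating is biased upward if dissatisfaction drives dropout. Session ratings, attrition and adherence reduce the problem but do not remove it.

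The size cannot be determined from the document. It is the proportion of adolescents stopping during the sessions times the finisher–stopper gap: 0 to 0.34 points at an assumed 20% stopping and gaps of 0 to 1.7. The number of adolescents, the timing of attrition, the ratings and the 1–5 scale for the overall rating are all assumptions. The bias may be zero, but as described the plan could not show this for the overall rating. This is worth changing because the change is cheap and the missing answers cannot be recovered afterwards.

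**What to change.** In Instruments, tie the overall rating to the end of participation and not to the final session. Send it to every adolescent who attended at least one session, and at the time of stopping for those who leave early. Limit the ranking to sessions attended. Add one optional item on the main reason for stopping, if the full protocol does not already record it.

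In Data preparation and statistical analysis, name the overall rating among the acceptability measures. Report it for finishers and stoppers together and separately, with the number sent and the number answered in each group.

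The cost is one extra text-message trigger and at most one extra item. Some stoppers will not reply, so the bias may be reduced but not removed; this is why the response rates need to be shown.
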